Balance is an important foundation for independent daily functioning (3, 7, 8), and is a major training component in fall prevention programs (1–4, 9). Ineffective balance compensatory (reactive) reactions following an external-induced unexpected loss of balance such as a push, slip, or trip is one of the major causes of falls in older adults (9). Unexpected loss-of-balance situations trigger reactive balance responses which act to restore equilibrium, these responses depend on the size, type, and direction of the perturbation (10–12). Fixed base-of-support (BoS) strategies (feet remaining in place) are used to restore balance with ankle, hip, trunk, and arm movements during minor-to-moderate unexpected perturbation magnitudes, whereas at larger balance perturbations, change of BoS strategies such as a stepping response are used (9). When balance is unexpectedly lost, a quick reactive step can prevent a fall from occurring (9); however, it was also found that hip, trunk, and arm movements are also part of reactive stepping reactions (9, 12–15). A recent laboratory study of 83 older adults with varying histories of falls who were exposed to a wide range of perturbation magnitudes found that about 61% of these resulted in fixed BoS balance reactions without the need to recover balance by stepping (15). In fact, by using hip, trunk, and arm movements, the older adults were able to decelerate the center of mass (CoM) movement over the BoS, which may result in an ability to perform balance recovery steps at a higher perturbation magnitude, i.e., higher step threshold. A low step threshold was previously shown to be an independent predictor of a future fall (16–21).

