The compensatory step execution test examines reactive balance responses following unexpected platform translations. Perturbations are induced through a mechatronic device that provides controlled and unexpected AP and ML platform surface translations during standing and waking (46). For standing, participants are instructed to stand with feet placed together (heels and toes touching), resting arms naturally at their sides. For walking, participants are instructed to walk at their preferred treadmill walking speed with their hands free to swing (no handrails on the treadmill). Perturbations are synchronized to the initial contact phase of the gait cycle using the three-dimensional (3D) Vicon Motion System (Oxford, UK) and a code written in Mathlab for calculating the subject's own treadmill speed and step width. In standing as well as walking, participants are exposed to random of onset and random right/left/forward/backward unannounced platform translations that are increased systematically and controlled at ten perturbation magnitudes in increasing levels of difficulty. Four directional perturbations (right/left/forward/backward) occur in a random order at each level for a total of 40 perturbation trials (see Table 3 for perturbation details). During examination, participants wear a safety harness that prevents falls, but does not otherwise restrict their recovery balance movements. Falls during the assessment session are defined, as load cell sensors detect 30% or more of body weight suspended by the safety harness (48). Participants wear their own walking shoes and are instructed to react naturally to keep their balance and to prevent themselves from falling in response to perturbations. The increase in perturbation difficulty is adjusted by the examiner according to each subject's ability to recover. In case the subject should fall, grasp the examiner's hand, or ask to stop the test, the examination is stopped and will not continue to the next level. A seated rest break is given whenever needed. The data are analyzed observationally and kinematically for each trail.

**Table 3 T3:** Magnitude of the perturbation i.e., the parameters during the examination protocol of balance reactive response in standing.

**Perturbation size**	**Platform displacement (cm)**	**Perturbations velocity (m/s)**	**Perturbations acceleration (m/s^**2**^)**	**Perturbations random order**
Level 1	3	0.06	0.09	B, R, F, L
Level 2	4	0.06	0.18	B, F, R, L

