#### Kinematic Analysis

3D kinematic data are collected through optical motion capture (Vicon Motion Systems, Oxford, UK), providing kinematic analysis of a motion sequence. Sixteen infrared cameras cover the lab space, mounted at a height of 2.6 ± 0.2 meters and providing a capture volume of 5.5 × 1.2 × 2.0 m^3^ evenly scattered approximately four meters around the treadmill. The cameras operate and sample simultaneously, at a frequency of 200 Hz, the location of 39 reflective markers placed on anatomical landmarks of the body and another two on the moving platform. The markers are attached to a prepared whole-body flexible suit that comes in several sizes to properly fit each subject. Views from the 16 cameras are mapped onto a 3D coordinate system by the computer (Vicon Systems software) using an internal direct linear transformation algorithm. Perturbations that are followed by execution of a compensatory step (change in BoS) are digitized, transformed, and smoothed using a low-pass filter (Butterworth second-order forward and backward passes) with a cut-off frequency of 5 Hz. The Vicon system was shown to be valid and reliable. Overall trueness (systematic deviations) of a dynamic reference object was −0.23 ± 0.35 mm (−0.24 ± 0.36%) and overall uncertainty (random deviations) for dynamic measurements was 1.11 ± 0.94 mm (1.16 ± 0.99%). For lower body assessment (10 cameras, foot region) during walking, the mean trueness and uncertainty was 0.08 and 0.33 mm, respectively (47).

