The following kinematic parameters are extracted: (1) the step initiation duration in milliseconds (ms) is calculated as the time from surface horizontal translation to step initiation, (2) first recovery stepping duration (ms) is calculated as the time from surface translation to foot-contact on the ground, (3) first compensatory step length is calculated as the Euclidian distance in centimeters (cm) that the ankle markers are displaced from step initiation to first step recovery, and (4) Margin of Stability (MoS), which is the distance between a velocity adjusted or “extrapolated” position of the CoM (XcoM) and the edge of an individual's BoS at any given instant in time. The MoS is directly related to the impulse (I) required to cause instability (49). When a participant takes extra steps to recover balance, i.e., a multiple-step reaction, the following parameters are determined: total balance recovery duration (ms), which is the time from surface translation to foot contact on the ground, completing multiple steps to recover balance; recovery step path length, which is the Euclidian distance in cm that the ankle markers are displaced from step initiation to foot contact on the ground, completing full balance recovery; and total CoM path displacement (cm), defined as the distance in cm of the CoM traveled from the initial point prior to stepping to the point where participants completed their full balance recovery. Using this method, Batcir et al. (14) found excellent inter-observer reliability for observational and kinematic analysis.

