### Sample Size Estimation

Sample size requirements were calculated using PS power calculation software (66). Because the aim of the study is to examine the effect of perturbation-based bicycle training on various aspects of balance control, well-known parameters that reflect reactive, proactive, and standing postural balance control were selected. Calculations were performed separately to determine sample size requirements based on a single-step threshold in standing (reactive balance), voluntary step execution (i.e., foot contact time) (proactive balance), and ML postural sway (standing postural control), all reflective of unsteadiness in balance control between older and younger adults (13, 14, 50, 55, 58, 67, 68) and between fallers and non-fallers (13, 15–21, 55–58, 60). Type I error probability of 0.05 and Type II error probability of 0.2 was applied for the three two-sided test calculations. Based on our preliminary results, the compensatory single-step threshold in standing was 10.8 cm of lateral translation in older adults with bicycle riding habits compared to 7.9 cm in age- and gender-matched controls [data in processing], the ML postural sway in EO was 30.6 mm in older adults with bicycle riding habits compared to 38.8 mm in controls (31), and the step execution times (i.e., foot contact time) in single-task condition of older bicyclists were 104 ms less than those of the controls (921 vs. 1,025 ms) (30). Using net reduction values (2.9 cm, 8.2 mm, and 104 ms, respectively) in combination with the initial variance estimates (standard deviations of 3.45 cm, 7.8 mm, and 134 ms, respectively), it was determined that 27 participants per group would be required. To account for reported attrition rates of about 25% in studies involving older adults (69), we decided to include about 34 participants in each group for a total of 54 (27 × 1.25 = 34).

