### Statistical Analysis

PASW Statistics version 26.0 are used for statistical calculations. Baseline characteristics are compared using independent *t*-tests and Mann–Whitney *U*-tests for continuous and ordinal variables, respectively. Descriptive data analysis and tests for the assumptions of normality (Shapiro-Wilk's statistic) are followed by a two-way repeated measure analysis of variance (ANOVA) for within subjects (pre- vs. post-tests) and between groups (experimental vs. control groups). The primary outcome variables are the single-step and multiple-step thresholds, the first-step recovery initiation duration, first step duration, total balance recovery duration, and the MoS. These variables were previously found to be able to distinguish between younger and older adults (14) and between fallers and non-fallers (15). The single-step threshold was previously shown to be an independent predictor of a future fall (16–21) and to reflect unsteadiness in reactive balance control among older adults with varying histories of falls (15). The secondary laboratory outcome variables are foot contact time (voluntary stepping), and the ML CoP sway, as well as SDA parameters (Cd and Ds). All these parameters were previously found to reflect unsteadiness in balance control (13, 50, 55, 56, 58, 67, 68) related to falls (13, 55–58, 60), and also related to older adults who have bicycle riding habits (30). The other secondary outcome measures are the BBS, 6MWT, LLFDI, and FES-I. An intention to treat analysis is conducted by carrying the last obtained measurements forward for those participants who do not complete all aspects of the study. The significance level is *p* < 0.05.

The effect size (ES) (Hedge's g) between the two independent groups is calculated by dividing the difference between the means of each group by the pooled baseline standard deviation of both groups. Values between 0.2 and 0.49 are considered small, between 0.5 and 0.79 moderate, and 0.8 and higher is considered a large effect. In addition, for each outcome parameter, we explore whether a minimal detectable change has been reached. As data will be analyzed at the end of the study, there is no plan for interim analyses of primary and/or secondary variables.

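### Kinematic primary outcomes come only from trials that provoked a step and are analysed without perturbation level, so a training effect on the step threshold would mix them with perturbation size

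*Protocol article*

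**What the plan says.** All references are to the Protocol article.

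- **Test (Primary Outcome Measures).** Platform translations are "increased systematically and controlled at ten perturbation magnitudes in increasing levels of difficulty", with four directions per level. The test ends when the participant falls, grasps the examiner's hand or asks to stop.
- **Trials processed (Kinematic Analysis).** "Perturbations that are followed by execution of a compensatory step (change in BoS) are digitized".
- **Definitions (Kinematic Analysis).** The timing variables run to step events; for example, "the step initiation duration in milliseconds (ms) is calculated as the time from surface horizontal translation to step initiation". Total balance recovery duration and total CoM displacement belong to a smaller set: "When a participant takes extra steps to recover balance, i.e., a multiple-step reaction, the following parameters are determined".
- **Outcomes (Statistical Analysis).** "The primary outcome variables are the single-step and multiple-step thresholds, the first-step recovery initiation duration, first step duration, total balance recovery duration, and the MoS". Four of these six are kinematic. Primary Outcome Measures lists total CoM displacement where this sentence has MoS.
- **Model (Statistical Analysis).** A "two-way repeated measure analysis of variance (ANOVA) for within subjects (pre- vs. post-tests) and between groups (experimental vs. control groups"). Neither perturbation level nor direction appears.
- **Expected effect.** The Introduction says that hip, trunk and arm movements decelerate the CoM, "which may result in an ability to perform balance recovery steps at a higher perturbation magnitude, i.e., higher step threshold". Sample Size Estimation uses a threshold contrast: "the compensatory single-step threshold in standing was 10.8 cm of lateral translation in older adults with bicycle riding habits compared to 7.9 cm".

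**The concern.** Whether a trial enters the kinematic analysis is decided after randomisation, by whether the participant stepped. Stepping is also what the threshold, another primary outcome, measures. If training works as the Introduction proposes, trained participants at T2 step only at larger translations, while controls still contribute steps at smaller ones. The upper end can move as well, because a participant who recovers better goes further before the test stops.

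A model with only time and group has no means of separating a change in how people recover from a change in the size of the push. The kinematic outcomes could then show a difference when recovery at any given level is unchanged, or hide one when it has changed.

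**Working it through.** **1. The planning effect.** With two-sided alpha 0.05 and power 0.80, n per group = 2(1.960 + 0.842)² × (SD/difference)² = 15.70 × (SD/difference)².

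- Single-step threshold: 15.70 × (3.45/2.9)² = 22.2, so 23.
- ML sway: 15.70 × (7.8/8.2)² = 14.2, so 15.
- Foot contact time: 15.70 × (134/104)² = 26.1, so 27.

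The largest is 27, which reproduces the stated figure. The 2.9 cm threshold difference is therefore a working assumption of the plan, and it is used below.

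**2. Where the planning thresholds fall on Table 3 (linear interpolation).**

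- 7.9 cm lies between level 5 (7 cm) and level 6 (8 cm): level 5.9. Velocity is 0.22 + 0.9 × 0.11 = 0.32 m/s, and acceleration 0.7 + 0.9 × 0.4 = 1.06 m/s².
- 10.8 cm lies between level 7 (9 cm) and level 8 (12 cm): 7 + 1.8/3 = level 7.6. Velocity is 0.44 + 0.6 × 0.22 = 0.57 m/s, and acceleration 1.5 + 0.6 × 0.5 = 1.80 m/s².

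The difference is 7.6 − 5.9 = 1.7 levels.

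**3. Average stimulus over stepping levels.** Assume a step at every level at or above the threshold, and that all higher levels are completed. The lowest level delivered at or above 7.9 cm is level 6; at or above 10.8 cm it is level 8.

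| Stepping levels | Displacement (cm) | Velocity (m/s) | Acceleration (m/s²) |
|---|---|---|---|
| 6 to 10 | 62/5 = 12.4 | 3.51/5 = 0.70 | 10.1/5 = 2.02 |
| 7 to 10 | 54/4 = 13.5 (+9%) | 3.18/4 = 0.795 (+13%) | 9.0/4 = 2.25 (+11%) |
| 8 to 10 | 45/3 = 15.0 (+21%) | 2.74/3 = 0.91 (+30%) | 7.5/3 = 2.50 (+24%) |

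The last row overstates the planning effect somewhat, because the grid jumps from 9 to 12 cm and turns 1.7 levels into two. With thresholds spread around their means (step 5), the average gap in displacement is about 1.9 cm rather than 15.0 − 12.4 = 2.6 cm.

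**4. From stimulus to bias.** If an outcome changes by b per level and training has no effect at any fixed level, the spurious arm difference is about b × (difference in mean level). Averaged over stepping trials, mean levels are 8 (levels 6 to 10) and 9 (levels 8 to 10), so the bias is about 1 × b. Taken at each person's own threshold, it is about 1.7 × b. The documents do not give b.

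**5. Illustration only.** Simulation with 27 per arm and 1,500 runs per setting. From the plan: T1 threshold mean 7.9 cm, SD 3.45 cm, and a 2.9 cm shift in one arm. Assumed: pre-post correlation 0.7, between-person and trial SDs of 60 ms, and the slopes shown. The test is a t-test on change, equivalent to the group-by-time test with two visits. There is no true effect at any level.

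| Slope (ms per level) | All stepping trials: bias, rejection | Own threshold: bias, rejection | One common level: rejection |
|---|---|---|---|
| 0 | 0 ms, 5% | 1 ms, 5% | 5% |
| −10 | −9 ms, 11% | −18 ms, 12% | 5% |
| −20 | −18 ms, 26% | −36 ms, 28% | 6% |
| −40 | −36 ms, 56% | −72 ms, 59% | 5% |
| +20 | +18 ms, 27% | +35 ms, 26% | 5% |

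A second simulation used other assumptions: T1 threshold level with mean 6 and SD 1.3, visit SD 20 ms, trial SD 30 ms, and slopes of −5, −10 and −20 ms. It gave 8%, 16% and 45% for a two-level shift, and 7%, 8% and 17% for a one-level shift. The pattern agrees; the percentages depend on the inputs.

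**The case against.** The strongest reply is that the article never says how trials become one value per participant. Averaging over stepping trials is an inference, and an analysis plan not shown might compare the arms at one common level, which would remove the size imbalance. This stands as a limit. It does not dispose of the point, because the selection rule and the model are both stated, and the two natural summaries (all stepping trials, or the person's own threshold) both give a confounded contrast. Primary Outcome Measures does say in general terms that every trial is analysed kinematically, but Kinematic Analysis is the specific rule, and step timing cannot exist without a step.

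Other objections also hold in part:

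- The planning contrast is lateral, in standing, and between habitual cyclists and controls. It is not a pre-post change in four directions. Table 3 covers standing only, so the walking test cannot be quantified.
- Total recovery duration and total CoM displacement depend on the multiple-step threshold, so the figures above do not describe them directly.
- A level term does not undo the selection. At a level where many trained participants no longer step, those who do are a subset formed after randomisation.

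A reader might infer that the trial has a type I error of 45% or 56%, or that an ineffective training could be made to look effective. The documents support neither. Those rates rest on assumed slopes and SDs, and if training shifts neither the thresholds nor the stopping point, this mechanism produces no bias.

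**Conclusion.** The concern holds in a limited form. As written, the kinematic primary outcomes are conditional on stepping, or on multiple stepping, and the stated model ignores perturbation size. With a threshold effect like the one used for planning, about 1.7 levels of Table 3, the arms at T2 would be compared at clearly different stimuli: up to 12.4 against 15.0 cm and 0.70 against 0.91 m/s, if all higher levels are completed. A shift in the stopping point would add to this and is not counted here.

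The effect on the outcomes is of unknown sign and size. It is zero where the outcome does not vary with level and grows with that slope. It would be wrong to conclude that all primary outcomes are compromised: the single-step and multiple-step thresholds are unaffected. What cannot be done is to read a kinematic difference as a change in the quality of recovery when the threshold has also moved.

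**What to change.** 1. For the kinematic outcomes, replace the two-factor ANOVA by a trial-level mixed model with arm, visit, arm-by-visit, perturbation level and direction as fixed effects and a random participant effect. Report the arm contrast at a common level.
2. Give equal prominence to an analysis restricted to levels at which nearly all participants in both arms step at both visits, since the level term alone does not remove the selection on stepping.
3. Compute MoS on all delivered trials, keeping the level term because the number of levels delivered still depends on ability.
4. Keep total CoM displacement and total recovery duration as defined for multiple-step reactions, with the same level adjustment. By their definitions they do not exist on non-stepping trials.
5. State that the step-timing and multiple-step variables are conditional on stepping and are supportive of the threshold outcomes.

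The cost is a somewhat more complex model, added wording, and extra processing of existing recordings. No new participants or visits are needed.

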**ASSESSMENTS**					
**Primary outcome measures**					
***Reactive balance control***—**Compensatory Step Execution tests during standing and walking** (single-step and multiple-step thresholds, first-step recovery initiation duration, first step duration, total balance recovery duration, total CoM displacement).			X		X

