### Primary Outcome Measures

Because this study deals with the ability to learn and generalize reactive balance responses that are acquired in a sitting position into a target context of fall risk factors and balance control performances in standing and walking situations, our primary outcome measures to evaluate the effect of PBBT during bicycle riding are derived from the ability to recover from unexpected external perturbations in the compensatory step execution tests during standing and walking. The best observational and kinematic measures to represent the reactive (compensatory) balance responses are: the single-step and multiple-step thresholds (observational parameters), and the first-step recovery initiation duration, first step duration, total balance recovery duration, and total CoM displacement (kinematic parameters) (14). All of these parameters have been previously found to be able to distinguish between younger and older adults (14) and fallers and non-fallers (15). The single-step threshold was previously shown to be an independent predictor of a future fall (16–21) and to reflect unsteadiness in reactive balance control among older adults with varying histories of falls (15). Moreover, excellent inter-observer reliability has been reported for single-step and multiple-step thresholds (ICC_2, 1_ = 0.978 and ICC_2, 1_ = 0.971, respectively; *p* < 0.001), and for first-step recovery initiation duration, first step duration, total balance recovery duration, and total CoM displacement (ICC_2, 1_=0.917, ICC_2, 1_=0.975, ICC_2, 1_=0.950, and ICC_2, 1_=0.918, respectively; *p* < 0.001) (14).

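### Total balance recovery duration and total CoM displacement are determined only after a multiple-step reaction, so their T2 comparison is selected on response to the training

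*Protocol article*

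**What the plan says.** Kinematic Analysis in the protocol article has two lists. The first covers trials with a compensatory step: step initiation time, time to first foot contact, first step length and margin of stability (MoS). The second is conditional: "When a participant takes extra steps to recover balance, i.e., a multiple-step reaction, the following parameters are determined: total balance recovery duration (ms". It also contains recovery step path length and "total CoM path displacement (cm), defined as the distance in cm of the CoM traveled from the initial point prior to stepping". The duration is defined as ending when the multiple steps are completed. The same section limits processing to stepping trials: "Perturbations that are followed by execution of a compensatory step (change in BoS) are digitized".

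The outcomes have this status:

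- Table 1 lists as primary "first step duration, total balance recovery duration, total CoM displacement".
- Primary Outcome Measures lists "first-step recovery initiation duration, first step duration, total balance recovery duration, and total CoM displacement (kinematic parameters".
- Statistical Analysis lists "first step duration, total balance recovery duration, and the MoS", so recovery duration stays and MoS stands where CoM displacement stood.

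The analysis is a "two-way repeated measure analysis of variance (ANOVA) for within subjects (pre- vs. post-tests) and between groups (experimental vs. control groups". Last-observation-carried-forward is planned for participants who do not complete the study.

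**The concern.** Whether a participant takes several steps at T2 is a result of treatment. The multiple-step threshold, itself a primary variable, measures exactly that. An outcome that exists only in multi-step trials is therefore observed in a subset chosen by response, and the groups compared at T2 are no longer the randomised groups.

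This can happen in two ways. A participant with no multi-step trial at T2 has no value for either variable. A participant who improves but still multi-steps does so at higher perturbation levels, so the T2 value may come from a harder test than the T1 value. In both cases a move from several steps to one at a given level is not recorded as a gain on these outcomes. At stake is a valid reading of one primary outcome in every listing, and of a second in two of the three.

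**Working it through.** **1. Which recoveries yield a value**

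| Recovery in a trial | First step duration | Total recovery duration | Total CoM displacement |
|---|---|---|---|
| Feet in place | none (trial not digitized) | none | none |
| One step | yes | none | none |
| Several steps | yes | yes | yes |

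Nothing in the article gives the last two columns a value in the first two rows, or fixes the level at which T1 and T2 are compared.

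**2. The carry-forward rule.** It addresses non-completers. A participant who completes T2 but has no multi-step trial is not one. If the rule were stretched to that person, the T2 value would be set to the T1 value and the change would be 0, so an improver would be scored as unchanged.

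**3. The plan's own sample size.** Inputs from Sample Size Estimation: two-sided 0.05, power 0.80, n per group = 2(1.960 + 0.842)²(SD/difference)².

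- Foot contact time, 104 and 134 ms: 15.70 × (134/104)² = 26.06, so 27.
- Single-step threshold, 2.9 and 3.45 cm: 22.2, so 23.
- ML sway, 8.2 and 7.8 mm: 14.2, so 15.

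The stated 27 reproduces as the largest of the three. None of them concerns the two outcomes at issue, and none allows for undefined values.

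**4. Loss of numbers alone.** As a stand-in, take the effect behind the 27: 104/134 = 0.776 SD. Power = Φ(0.776√(n/2) − 1.96). The share with a value is assumed equal in both arms.

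| Share with a T2 value | n per arm | Power |
|---|---|---|
| 100% | 27 | 0.81 |
| 90% | 24.3 | 0.77 |
| 80% | 21.6 | 0.72 |
| 70% | 18.9 | 0.67 |
| 60% | 16.2 | 0.60 |
| 50% | 13.5 | 0.52 |

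**5. Selection at one fixed level.** Assume a normal latent recovery measure with SD 1, multi-stepping when it exceeds a cut-off c, and a shift of −δ in the experimental arm. The mean among multi-steppers is μ + φ(c − μ)/[1 − Φ(c − μ)].

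Worked case: 80% of controls multi-step, so c = −0.842, and δ = 0.5.

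- Control mean: 0.280/0.800 = 0.350.
- Experimental mean: −0.5 + 0.376/0.634 = 0.094.
- Difference: 0.256 SD, or 51% of the true 0.5 SD.

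| Controls multi-stepping | Experimental multi-stepping (δ = 0.5) | Difference seen | Share kept, δ = 0.5 | Share kept, δ = 0.776 |
|---|---|---|---|---|
| 90% | 78% | 0.32 SD | 64% | 60% |
| 80% | 63% | 0.26 SD | 51% | 48% |
| 70% | 51% | 0.21 SD | 43% | 40% |
| 50% | 31% | 0.16 SD | 31% | 29% |

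**6. Selection in the graded test.** Assume that all ten levels are completed, that multiple-step thresholds have mean level 7 and SD 1.5, and that the experimental arm gains 2 levels. A value exists if the threshold is at most 10.

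- Control: Φ((10 − 7)/1.5) = Φ(2) = 0.977, about 26 of 27.
- Experimental: Φ((10 − 9)/1.5) = Φ(0.667) = 0.748, about 20 of 27.

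Now take one participant who moves from threshold 7 to 9 and whose multi-step trials are averaged (the article states no aggregation rule). Multi-step levels are 7 to 10 at T1 (mean 8.5) and 9 to 10 at T2 (mean 9.5).

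- If duration rises b ms per level, the recorded mean worsens by (9.5 − 8.5)b = b.
- If duration rises b ms per level above the person's own threshold, the mean excess falls from (0+1+2+3)/4 = 1.5 to (0+1)/2 = 0.5, and the recorded mean improves by b.
- An equal mix of the two shows no change.

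In none of these is the real gain, one step instead of several at levels 7 and 8, counted. The documents give no value for b.

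**The case against.** The strongest reply is that the test is graded. The primary-outcome section describes ten rising magnitudes in four directions, up to 40 trials, in standing and in walking. Someone who stops multi-stepping at a middle level goes on to harder ones and may well multi-step there. This stands. A reader might infer that every improver drops out and that the analysis keeps only unimproved participants. The documents do not support that: complete loss affects only those with no multi-step trial at all, and no frequency is given.

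A reader might also infer that the effect is always pulled to zero. A model that makes each participant either a multi-stepper or a one-stepper, and gives those who stay multi-steppers no benefit, returns zero by construction. Step 5 gives partial attenuation, and step 6 shows that the sign can go either way.

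It is also true that the move from several steps to one is captured elsewhere. The multiple-step threshold is primary, and the reactive-balance sample size calculation rests on the single-step threshold. That limits the damage to the trial as a whole, but does not repair the two outcomes.

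Finally, aggregation over trials and handling of missing values are often left to an analysis plan. The condition itself is not: the article fixes it, and a plan that followed it faithfully would inherit the selection.

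**Conclusion.** The point holds in a limited form. Recovery duration (primary in all three listings) and CoM displacement (primary in two) are determined only in multi-step trials, so their T2 comparison is conditioned on a response that the training is meant to change. Some participants may have no T2 value, and others may contribute values from harder perturbations than at T1.

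The size is unknown, because the documents give neither multi-step frequencies nor the relation between duration and level. The illustrations rest wholly on assumed inputs. They show that the rule can keep roughly 29% to 64% of a real benefit, erase it or reverse it. The step thresholds are not affected in this way. The disagreement over CoM displacement and MoS is a separate inconsistency that bears on how many primary outcomes are touched.

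**What to change.** 1. In Kinematic Analysis, define both variables for every stepping trial. For a one-step recovery, total recovery duration equals the time to first foot contact, which is already extracted, and CoM displacement runs to that point.
2. Compare T1 and T2 at the same prespecified perturbation level and direction. Scoring all trials without this would keep the harder-level distortion.
3. State one rule for no-step trials at that level, for example ranking them as the best outcome in a rank-based analysis. Without it, recovery duration stays undefined for feet-in-place recoveries. State also how a level that was not reached is handled.
4. Keep the multi-step-only values as descriptive.
5. Reconcile Statistical Analysis with Table 1 and Primary Outcome Measures on whether CoM displacement or MoS is primary.

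The cost is some extra processing of data already captured, with no added visit or test. On one-step trials total recovery duration will coincide with first step duration, another primary variable. Results will be less directly comparable with earlier multi-step-only reports, which item 4 eases.
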